### Outcomes and measures

#### Participant timeline

Participants in the intervention group and control group will be assessed at the preintervention baseline (T0), at the end of the 12-week intervention (T12), and at follow-up 24 weeks after baseline (T24). A physiotherapist and an occupational therapist (Researchers 4 and 5) who are blinded to group allocation will perform all the assessments. All participants will maintain contact with Researcher 3 throughout the follow-up period through the web software, email, and telephone. Table 1 shows the schedule of enrollment, interventions, and assessment according to the SPIRIT guidelines [42].

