### Sample size and statistical analyses

The sample calculation was performed using the GPower v.3.1 program [60]. Two outcomes of extreme functional importance for patients with DPN were used to calculate the sample size. Considering the primary outcome (DPN symptoms), a medium effect size (0.52) was adopted and, for the secondary outcome (peak pressure at forefoot), a small effect size (0.20) was adopted. Both effect sizes were taken from the study by Sartor et al. [30] which evaluated the effect of a 12-week supervised physical therapy exercise in patients with DPN. In order to obtain the largest sample size, the smallest effect size (0.20) was used. A statistical design of F-test repeated measures and interaction between and within factors with two repeated measures and two study groups, a statistical power of 0.80, an alpha of 0.05, and an effect size of 0.20 were used for the sample size calculation. The resulting sample size was 52 individuals. A final sample size of 62 patients was then chosen after estimating a drop-out rate of 20%.

The inferential statistical analysis will be based on an intention-to-treat analysis and per-protocol analysis. Mixed general linear models of analysis of variance for repeated measure will be used to detect treatment–time interactions (α = 5%), and the Newman–Keuls post hoc test will be used to obtain group effect (intervention group and control group), time effect (between T0 and T12), and group–time interaction. Effect sizes (Cohen’s *d* coefficient) will also be provided between T0 and T12 and between T12 and T24 to determine if the intervention shows any treatment effect. The difference between the means with their respective 95% confidence intervals will also be calculated. Imputation of any missing data for the analyzed variables will be conducted depending on the nature of the losses: missing completely at random, missing at random, or missing not at random. The per-protocol analysis will include only those patients who completed follow-up in the allocated intervention group. If there is evidence that the difference in the treatment depends on certain patient characteristics identified in the baseline assessment, a subgroup analysis will be performed.

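### The group-by-time test compares change scores and leaves the T0 value unused as a covariate: valid, but at the correlation implied by N = 52 it gives up a quarter of the information

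*Protocol article*

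**What the plan says.** In the protocol article, the section Sample size and statistical analyses fixes the model: "Mixed general linear models of analysis of variance for repeated measure will be used to detect" treatment-by-time interactions at the 5% level. Newman–Keuls post hoc tests follow for group, for time (T0 to T12) and for the interaction. Cohen's d is given for T0–T12 and T12–T24, and mean differences come with 95% confidence intervals. The only other use of baseline data in the analysis is a conditional subgroup analysis.

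The sample size rests on the same kind of test, an "F-test repeated measures and interaction between and within factors with two repeated measures and two study groups". The inputs are "a statistical power of 0.80, an alpha of 0.05, and an effect size of 0.20 were used for the sample size calculation". On the choice of effect size the section says "In order to obtain the largest sample size, the smallest effect size (0.20) was used"; that value belongs to a secondary outcome, forefoot peak pressure. The result is given as "The resulting sample size was 52 individuals", raised to 62 for drop-out.

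Participant timeline schedules assessments at T0, T12 and T24, and the abstract says that all outcomes are measured at each. So every outcome has a baseline value.

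**The concern.** When T0 is one level of the time factor, the group-by-time contrast between T0 and a later visit is the difference between arms in mean change. A change score subtracts the whole baseline value, as if it carried forward one for one. Regression on T0 subtracts only the part that predicts follow-up, so its residual variance is smaller whenever the correlation is below 1. In a trial of 62 patients, precision that can be had from data already collected is worth taking.

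The second issue is the number of visits. The powered test has two measures and one degree of freedom, while the trial has three visits. A single interaction over three visits is a different test, and it does not say which visit carries the primary comparison.

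**Working it through.** **Inputs.** From Sample size and statistical analyses: f = 0.20, alpha 0.05, power 0.80, two groups, two measures, N = 52, drop-out 20%, final N = 62. The correlation rho is not stated.

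**1. Reproduce N = 52.** For the within-between interaction, lambda = f² × N × m / (1 − rho), with 1 and N − 2 degrees of freedom for m = 2. At rho = 0.50, lambda = 0.04 × 52 × 2 / 0.50 = 8.32 on 1 and 50 df, and power is 0.8075. The smallest even N that reaches 0.80 is 52, as stated. Other correlations give N = 62 (rho 0.40), 56 (0.45), 54 (0.49), 52 (0.51), 50 (0.52) and 42 (0.60). The stated N therefore implies rho of about 0.50.

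**2. Put the effect on the SD scale.** In a 2 × 2 layout, f = 0.20 is a difference between arms in mean change of 4 × 0.20 = 0.80 SD. Check: lambda = (N/4) × 0.80² / [2(1 − rho)] = 13 × 0.64 / 1 = 8.32, the same value.

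**3. Compare variances**, assuming equal SD s at both visits:
- change score: 2(1 − rho)s²
- T0 as covariate: (1 − rho²)s²
- ratio of adjusted to change score: (1 + rho)/2, so the loss is (1 − rho)/2

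At rho = 0.50 these are 1.00s² and 0.75s²: ratio 0.75, loss 25%. A simulation of 20,000 trials with 26 per arm gave a ratio of 0.76, the small excess being the cost of estimating the slope. Both estimators averaged 0.80.

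**4. Power with adjustment at rho = 0.50.** Lambda = 13 × 0.64 / 0.75 = 11.09 on 1 and 49 df; power is 0.904 against 0.8075. For 80% power the adjusted analysis needs 39 patients (40 for equal arms) instead of 52. With 50 completers (62 × 0.80 = 49.6), power is 0.79 unadjusted and 0.89 adjusted.

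**5. Dependence on rho** (0.80 SD, N = 52):

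| rho | Loss | Power, change score | Power, adjusted |
|---|---|---|---|
| 0.3 | 35% | 0.667 | 0.842 |
| 0.5 | 25% | 0.808 | 0.904 |
| 0.7 | 15% | 0.955 | 0.977 |
| 0.8 | 10% | 0.994 | 0.997 |

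**6. Chance imbalance.** If the arms differ by D at T0, the expected follow-up difference is the treatment effect plus rho × D. Subtracting D leaves an error of −(1 − rho)D. With 31 per arm the standard error of D is √(2/31) = 0.25 SD. At rho 0.5, a gap of that size shifts the change-score estimate by −0.5 × 0.25 = −0.13 SD (rounded).

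**7. Three visits.** Assume compound symmetry, rho 0.5 and N = 52. The 2-df omnibus interaction has power 0.84 if the 0.80 SD effect is the same at T12 and T24 (lambda 11.09), and 0.72 if it halves by T24 (lambda 8.32). Neither is the 0.81 of the powered test.

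**The case against.** The strongest defence is that nothing here is invalid. A group-by-time interaction is a standard pre-specified analysis, it is unbiased under randomisation, and it matches the family used for the sample size. Covariates are often left to an analysis plan, which is not shown. The first part stands: this is a matter of efficiency. The second part weighs less, because the article does not leave the model open. It names the interaction test and powers the trial on it.

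It is also fair that 25% rests on a correlation solved from N = 52, in a calculation driven by a secondary outcome. The true correlations of the two primary outcomes are unknown, and at rho 0.7 or above the power gain for 0.80 SD is small. The size must stay conditional on rho; the direction does not depend on it.

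Three stronger readings are tempting, and the document does not support them:
- That the interaction carries a T0 imbalance fully into the estimate. The error is −(1 − rho) times the imbalance, which is half of it, with reversed sign, at rho 0.5.
- That the analysis answers neither the 12-week nor the 24-week question. The post hoc tests, the T0–T12 effect size and the confidence intervals speak to it. What is missing is one named primary contrast.
- That the trial is weakly powered for its primary outcome. The article says "Considering the primary outcome (DPN symptoms), a medium effect size (0.52) was adopted" without giving the scale. Read as f, like the 0.20, power at N = 52 is near 1 under either analysis. Read as a between-group difference of 0.52 SD, it is 0.45 without and 0.56 with adjustment, but that sets a d beside an f from the same paragraph.

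**Conclusion.** The point holds as one of efficiency and clarity. The planned interaction is unbiased but uses the T0 value less well than a covariate would, losing (1 − rho)/2 of the information. That is 25%, and power of 81% instead of 90%, at the correlation implied by the stated N; over rho 0.3 to 0.8 the loss runs from 35% to 10%. These figures assume equal SDs across visits, a common T0-to-follow-up correlation in both arms, 52 evaluable patients and the powered effect of 0.80 SD. The power figures are for a single-visit contrast, not the three-visit omnibus test. Separately, the omnibus test has 2 degrees of freedom, is not the one that was powered, and leaves the primary contrast unnamed. The rule on imputing missing data is a different question and is no part of this conclusion.

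**What to change.** Replace the primary model with a linear mixed model for the T12 and T24 values. Its terms are group, time, group-by-time, the participant's T0 value of the same outcome, and T0-by-time, with an unstructured covariance. Report the adjusted group difference with its 95% confidence interval at T12 (primary) and at T24. A constrained-baseline mixed model serves the same aim and is an acceptable alternative.

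Before T0 is used this way, settle when it is measured. Trial design places the initial blind assessment after group allocation. Participants and recruitment treats the laboratory eligibility visit as the baseline, and Randomization, allocation, and blinding puts screening before randomisation. These sections must be reconciled so that T0 is a true pre-randomisation value.

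The cost is a change of wording and two degrees of freedom, one for each T0 slope. No visit, measurement or patient is added.

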Education through software or booklets that provide guidelines for self-care and at-home exercises can be potentially successful alternatives to traditional treatments [38–40]. The accessibility of and advances in modern technology have made it possible to use electronic devices to improve adherence to health prevention and treatment, especially for chronic diseases [41].

Ferreira et al. [40] have developed and validated free, publicly available software, the Diabetic Foot Guidance System (SOPeD) (www.soped.com.br), with general guidelines on foot self-care and self-assessment and a personalized protocol including balance, strengthening, and stretching exercises for the treatment and prevention of the most common foot–ankle musculoskeletal deficits due to DM and DPN. This software is designed to provide and monitor exercises, facilitate self-care, and improve autonomous performance of daily living tasks [40]. However, its efficacy for the treatment of people with DM and DPN has not yet been proven and, to date, no studies have been performed to evaluate the effects of a rehabilitation technology capable of personalizing specific therapeutic foot exercises aimed at prevention and treatment of musculoskeletal deficits and complications in people with DPN.

The primary aim of this superiority randomized controlled, singe-blind, two-parallel-arm trial, the Footcare (FOCA) trial I, is to investigate the effects of the customized foot-related exercise software SOPeD on DPN symptoms and severity after 12 weeks (intervention completion) and 24 weeks (follow-up) in patients with DPN. The secondary aims are to investigate the effects of this intervention at 12 and 24 weeks on foot–ankle biomechanics and plantar pressure during gait, tactile and vibration sensitivities, foot health and functionality, foot strength, and functional balance.

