## Methods and design

### Trial design

This study is part of a series of two clinical trials: the FOCA trial I (SOPeD intervention) and FOCA trial II (booklet intervention). The FOCA trial I is a superiority, single-blind, randomized controlled trial with two parallel arms where participants will be randomized into one of two groups: the intervention group that will perform foot-related exercises included in the SOPeD; and the control group that will not receive any specific intervention besides the treatment recommended by a health care professional. This trial will have an allocation ratio of 1:1.

People with DM and DPN will be recruited from the Department of Endocrinology of the Hospital das Clínicas of the School of Medicine of the University of São Paulo, Brazil, and will be referred to a physical therapist who will perform the group allocation. The participants will then be referred to another physical therapist who will perform the initial blind assessment. All participants allocated to the intervention group will participate in a protocol of monitored and customized therapeutic exercises for the foot–ankle complex using the SOPeD software three times a week for 12 weeks [40]. After the 12-week period, the intervention group participants will be encouraged to continue exercising until the end of the study following the same schedule set during the intervention period. The participants allocated to the control group will not receive any specific intervention besides the regular treatment recommended by health care professionals (doctors, nurses, and podiatrists). If proven effective, the benefits of the foot-related exercise protocol will be explained and offered to all control participants at the end of the study.

All participants will be assessed at baseline, 12 weeks (end of intervention) and 24 weeks (follow-up). Assessments will record DPN symptoms and severity (primary outcomes) and all other secondary outcomes.

The Consolidated Standards of Reporting Trials (CONSORT) 2010 guidelines will be followed. The study was approved by a research ethics committee (CAAE: 90331718.4.0000.0065) and was registered at ClinicalTrials.gov on 8 July 2019 (study identifier NCT04011267).

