### Measures of primary and secondary outcomes

The quantification of DPN symptoms and classification of DPN severity will be the primary outcomes. Foot–ankle kinematics and kinetics during gait, plantar pressure distribution during gait, tactile and vibration sensitivities, foot health and functionality, foot strength, and functional balance constitute the secondary outcomes.

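### Two primary outcomes are each tested at 5% with no rule linking them (about 7–10% overall), and the post hoc test, Newman–Keuls, lacks strong error control over six means

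*Protocol article*

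**What the plan says.** All references are to the protocol article.

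- **Outcomes.** Measures of primary and secondary outcomes: "The quantification of DPN symptoms and classification of DPN severity will be the primary outcomes". The section on the fuzzy classification builds the severity score partly from the symptom instrument, so the two outcomes overlap.
- **Time points.** The primary aim in the Background concerns effects "on DPN symptoms and severity after 12 weeks (intervention completion) and 24 weeks (follow-up) in patients with DPN". Trial design: "All participants will be assessed at baseline, 12 weeks (end of intervention) and 24 weeks (follow-up"). Two arms at three visits give six group-by-time means.
- **Main test.** Sample size and statistical analyses: repeated-measures models "will be used to detect treatment–time interactions (α = 5"%).
- **Post hoc test.** Same section: the "Newman–Keuls post hoc test will be used to obtain group effect (intervention group and control group"), and also the "time effect (between T0 and T12), and group–time interaction". The text does not make this step conditional on a significant interaction and does not name the error term.
- **Sample size.** Same section: "a statistical power of 0.80, an alpha of 0.05, and an effect size of 0.20 were used for the sample size calculation". The 0.20 belongs to a secondary outcome, forefoot peak pressure. The section calls DPN symptoms the primary outcome, in the singular, and gives it an effect size of 0.52.

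The article gives no alpha split, testing order, main time point, or rule on whether one or both primary outcomes must succeed.

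**The concern.** There are two separate problems.

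First, with two primary outcomes each tested at 5% and no rule joining them, a trial that succeeds on either one can be reported as positive. The error rate for that claim is then above the stated 5%.

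Second, Newman–Keuls is a stated choice of method, not a detail left for later. It steps down through ranges of ordered means and uses a smaller critical value for shorter ranges. If all six means are truly equal, it holds 5%. If some truly differ and others do not, it need not. The pattern that matters here is both arms changing over time in the same way. The means then separate into three same-visit pairs, and each intervention-versus-control pair is compared at close to an unadjusted 5%.

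At stake is a claim of benefit at T12 or T24 that rests on the post hoc step or on whichever primary outcome happened to succeed. The Discussion says the sponsor intends to use the software in public health settings once effectiveness has been shown.

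**Working it through.** **1. The plan's own figure.** Inputs from the article: f = 0.20, 2 groups, 2 measures, alpha 0.05, power 0.80. Assumed, because not stated: within-patient correlation 0.5 and sphericity.

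- Noncentrality = f² × N × m / (1 − ρ) = 0.04 × 52 × 2 / 0.5 = 8.32, with 1 and 50 degrees of freedom.
- Power = 0.8075, so N = 52 reproduces.
- 52 × 1.2 = 62.4, stated as 62.

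The calculation therefore spends a full 5% on one test. The article states no familywise figure to reproduce.

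**2. Two interaction tests, either one counting as success.** If independent: 1 − 0.95² = 0.0975. For positively correlated tests, two-sided bivariate normal tail probabilities give:

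| Correlation between the two tests | Chance of at least one false positive |
|---|---|
| 0 | 9.75% |
| 0.5 | 9.1% |
| 0.7 | 8.4% |
| 0.9 | 7.0% |

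The article gives no correlation. The shared symptom instrument makes zero unlikely, so 9.75% is the upper end. Simulating the actual interaction F-tests gave similar values: 8.7–9.4% at outcome correlation 0.5 and 8.2% at 0.7.

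**3. Newman–Keuls over six means.** Assumptions: 26 per arm (52/2), within-patient correlation 0.5, pooled error term, no treatment effect, and the same time shifts in both arms. The result is the share of simulated trials with a false between-group difference at T12 or T24, per outcome.

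| Common shift at T0, T12, T24 (SD) | False T12 or T24 difference |
|---|---|
| 0, 0, 0 | about 1% |
| 0, −0.5, −0.5 | about 2% |
| 0, −0.3, −0.6 | about 3% |
| 0, −0.5, −1.0 | about 5–6% |
| 0, −0.8, −1.6 | about 10% |

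The last row agrees with theory. Once visits are well separated, each same-visit pair is tested at about 5%, and two post-baseline pairs give at most about 1 − 0.95² = 9.75%.

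**4. Effect of a gate.** If Newman–Keuls is run only after a significant interaction, the same T12-or-T24 rates fall to 2% or less at every trend above. The gate protects less when there is a real effect at T12 only, because the interaction is then significant. In a limiting case with a very large T12 effect, false T24 differences were about 4–5% per outcome and 8–9% over both outcomes.

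**The case against.** The strongest reply is that the confirmatory test is one interaction test per outcome, and that testing order and success rules are commonly left to an analysis plan that is not shown here. A post hoc test is also ordinarily run only after a significant omnibus result, and the trend needed for a 10% error rate is large: 1.6 SD in both arms by T24, including usual-care controls. Much of this stands. The article gives no basis for a trend of that size, and under a small trend or a gate Newman–Keuls does little harm. What does not fall away is that the article itself fixes Newman–Keuls, states no gate, and declares two primary outcomes at 5% each.

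A reader might infer stronger figures, which the document does not support:

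- **Four tests at 5%, giving 1 − 0.95⁴ = 18.5%.** The article does not specify separate 5% tests at each visit. It also sizes the trial on two measures, limits the named time effect to T0–T12 and calls week 24 follow-up.
- **12–14% from Newman–Keuls per outcome (ceiling 1 − 0.95³ = 14.3%).** This counts baseline pairs, and a baseline difference cannot be claimed as benefit.
- **About 36%, or repeated measures treated as independent means.** Both depend on how the test is implemented; the 36% needs a within-subject error term for between-group comparisons. The article names no error term.
- **Loss of power for the primary outcomes.** The 0.20 is a secondary-outcome effect. At the stated 0.52 for symptoms, power with 52 patients is at least 87% even at alpha 0.0125, whether 0.52 is read as d (f = 0.26) or as f.

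**Conclusion.** The point holds in a limited form. If success on either primary outcome is enough, the false-positive risk is about 7–10% instead of 5%. The figure depends on the unstated correlation, and the excess would vanish if both outcomes had to succeed, but no such rule is given.

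Newman–Keuls is a poor choice because it lacks strong familywise control over six means. The harm is conditional: about 1–2% per outcome with no or a small common trend, about 5–6% with a 1 SD trend by T24, about 10% with 1.6 SD, and 2% or less if gated on the interaction with no treatment effect. These rates rest on pooled error, 26 per arm and a within-patient correlation of 0.5. They support changing the method, but not a claim that the trial's error rate is well above 5% in every case.

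**What to change.** 1. Delete Newman–Keuls. Estimate the planned between-group contrasts at T12 and T24 from the mixed model, with confidence intervals, and apply Holm to any further pairwise comparison.
2. State how the primary outcomes are tested. One option is a fixed order at two-sided 5%: symptoms at T12 (the sample-size section already calls symptoms the primary outcome), then severity at T12, then symptoms and severity at T24, stopping at the first non-significant result. Holm across the two outcomes is an alternative.

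The change is to analysis wording only and should be made before the statistician is unblinded. The cost of the fixed order is that later steps cannot be claimed if an earlier one fails. The sample size is unchanged, because the first test keeps the full 5%. Under Holm, the smallest level for two outcomes is 0.025; at the stated symptom effect read conservatively (f = 0.26), power with 52 patients is still about 92%. The article gives no effect size for severity, so power for that outcome cannot be checked from it.

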#### Screening measures

An initial anamnesis will be performed to check the eligibility criteria, including clinical, anthropometric, and demographic characteristics of all participants. The classification of DPN severity will be determined using the Decision Support System for Classification of Diabetic Polyneuropathy [45, 46] (www.usp.br/labimph/fuzzy). Participants with scores ≥2.0 (mild DPN) will be included in the study. Those who score between 12 and 21 (probable depression) on the Portuguese version of the Hospital Anxiety and Depression Scale will not be included [47].

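### Cohen's d for T0–T12 and T12–T24 is given the job of showing a treatment effect, but it is not stated to compare the arms, and no listed contrast gives the 24-week effect against baseline

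*Protocol article*

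**What the plan says.** All of the analysis text is in the protocol article, Sample size and statistical analyses.

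- The inferential analysis is a mixed repeated-measures ANOVA aimed at treatment-by-time interactions, at a 5% level.
- Newman–Keuls post hoc tests follow for a group effect and for "time effect (between T0 and T12), and group–time interaction". T0–T12 is the only time contrast named.
- Cohen's d "will also be provided between T0 and T12 and between T12 and T24 to determine if the intervention shows any treatment effect".
- On mean differences, the section has a single sentence: "The difference between the means with their respective 95% confidence intervals will also be calculated". The text does not say whether these are means of arms or of time points.

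The Background section sets the primary aim as the effect on "DPN symptoms and severity after 12 weeks (intervention completion) and 24 weeks (follow-up) in patients with DPN". Trial design has every participant assessed at baseline, 12 and 24 weeks.

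Three other places bear on the point. Under Screening measures, "Participants with scores ≥2.0 (mild DPN) will be included in the study"; this is the fuzzy severity score, which is also a primary outcome. Participants and recruitment says that the laboratory visit confirming eligibility also serves as baseline. Trial design, Intervention group and Intervention all say that the intervention arm will be encouraged to keep exercising to week 24.

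**The concern.** The effect sizes are defined by time intervals, not by arms, yet they are assigned the task of showing whether treatment works. Two things follow.

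First, the second interval starts at T12. It measures gain or loss after the supervised period, not the effect at 24 weeks. The Discussion attributes the fading of earlier benefits to stopping exercise, and this trial tries to prevent that. If it succeeds, T12–T24 should be near zero, and the stated purpose of d would read the hoped-for result as no treatment effect.

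Second, if d is calculated within each arm, T0–T12 mixes treatment with natural course, retest and regression to the mean. The last is expected for the severity score, because patients enter on a minimum value of that score and the same visit supplies T0.

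**Working it through.** **1. The plan's own figure.** Stated inputs: two groups, two repeated measures, effect size 0.20 (taken as Cohen's f), alpha 0.05, power 0.80. The correlation between measures is not given; ρ = 0.5 is assumed. For the group-by-time interaction:

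λ = f² × N × m / (1 − ρ) = 0.04 × 52 × 2 / 0.5 = 8.32, with 1 and 50 degrees of freedom.

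Power is 0.8075, so N = 52 reproduces. (ρ = 0, 0.3 and 0.7 would give 102, 72 and 32.) The trial is therefore sized on a between-arm difference in change.

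The size of that difference follows. With ρ = 0.5 the SD of change is √(2 × 0.5) = 1 outcome SD. With 26 per arm the noncentrality is δ² × 26/2 = 13δ². Setting 13δ² = 8.32 gives δ = 0.8 SD.

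**2. What T12–T24 measures.** Take a between-arm difference of −0.8 SD at T12 (both primary scores are worse when higher) and three courses to T24:

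| Course after T12 | T0–T12 | T12–T24 | T0–T24 |
|---|---|---|---|
| Fully kept | −0.8 | 0.0 | −0.8 |
| Half lost | −0.8 | +0.4 | −0.4 |
| All lost | −0.8 | +0.8 | 0.0 |

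Only the last column is the 24-week effect, and it is not listed. These are between-arm values, so the gap does not depend on reading d as within-arm.

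**3. If d is within-arm.** Assume 26 per arm, SD of change 1, no treatment effect, and the same improvement in both arms. Results of 20,000 simulated trials, two-sided 5%:

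| Shared improvement (SD) | Intervention arm's own change significant | Significant in intervention arm only | Between-arm test of change |
|---|---|---|---|
| 0 | 5% | 5% | 5% |
| 0.2 | 17% | 14% | 5% |
| 0.3 | 32% | 22% | 5% |
| 0.5 | 69% | 22% | 5% |

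**4. Regression to the mean in the severity score.** For a score truncated below at z SD from the population mean, the expected fall on remeasurement is (1 − reliability) × φ(z) / (1 − Φ(z)). Reliability and the position of the cut are assumed:

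- z = −1, reliability 0.9: 0.1 × 0.242/0.841 = 0.029 SD.
- z = 0, reliability 0.7: 0.3 × 0.399/0.500 = 0.239 SD.

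The range is about 0.03 to 0.24 SD. It is expected equally in both arms, so it cancels in a between-arm difference in change and remains in a within-arm d.

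**5. The group effect.** Averaged over three times with no difference at T0, a constant effect E becomes (0 + E + E)/3 = 2E/3. An effect of 0.8 SD would appear as 0.53 SD.

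**The case against.** The strongest reply is that the plan does not rest efficacy on these effect sizes. The test is the treatment-by-time interaction, which compares the arms and keeps its 5% level when both improve equally, as the last column of the simulation shows. The d values are only an addition, with no significance threshold attached. This stands. A reader might infer that the trial would declare an effect from improvement in both arms; the document does not support that. The 17% to 69% belong to a paired test that the plan never names, under an assumed drift, and show only how misleading a within-arm reading would be.

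It can also be said that the within-arm reading is not settled, since d could be the between-arm difference in change over each interval. That too stands: it is the literal reading, not an established one.

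A reader might further infer that the plan never compares the arms at 24 weeks. That is not shown. T24 is assessed in everyone, the T0–T12 restriction is attached only to the time effect, and the model may include T24. The statement holds only for the listed contrasts.

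Finally, an article may leave detail to a fuller document, and T12–T24 is a sensible measure of maintenance. Both are fair, and the unspecified mean differences are not by themselves a finding. But the intervals and purpose of d are stated, not omitted, and the purpose does not fit T12–T24 on any reading. A reader could add between-arm differences for the two intervals to recover T0–T24. That requires a common scale, and adding would not give a confidence interval. A significant three-time interaction would not say when, in which direction or by how much the arms differ.

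**Conclusion.** The concern holds in a limited form. The main test is a proper between-arm test, and the sample size of 52 reproduces on that basis. What is badly fixed is the reporting attached to it: d is said to determine a treatment effect without being tied to an arm comparison, and none of the listed contrasts gives the effect at 24 weeks against baseline, although that time is in the primary aim.

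The 24-week part needs no assumption about which d is meant. A benefit fully kept gives T12–T24 = 0 whatever its size; the 0.8 SD used above rests on ρ = 0.5. The T0–T12 part is conditional: only a within-arm d carries the shared drift, including an assumed 0.03 to 0.24 SD of regression to the mean in the severity score.

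**What to change.** Replace the effect-size sentence with text to this effect:

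> The treatment effect is the between-group difference in change, with 95% confidence interval, from T0 to T12 and from T0 to T24, estimated from the group-by-time model. Cohen's d is computed on these between-group differences. Changes from T12 to T24 and changes within each arm are reported as descriptions of maintenance and course only.

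State also that the group main effect, which averages in T0, is not evidence of efficacy. The primary aim names 12 and 24 weeks together, so this change should not rank one above the other; any ranking should follow from the stated aim.

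The cost is a change of wording in the analysis text. All three assessments are already scheduled, so it needs no extra data, and the sample size does not change.
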